Although a number of compounds have been investigated to prevent or treat CIPN, none of them are sufficiently effective to be used routinely in clinical practice [15, 16]. Only duloxetine was recommended by ASCO and ESMO for neuropathic pain-related to CIPN [15, 16]. As a result of the lack of clear evidence, the current strategies used to reduce CIPN essentially consist in modifying of the chemotherapy doses and infusion schemes, although sometimes it continues to worsen despite stopping oxaliplatin. This aggravation can be linked to risk factors such as diabetes and excessive alcohol consumption. Little or no follow-up or treatment is offered to patients developing chronic neuropathy after their chemotherapy [10, 13, 17]. This leads to medical wandering, which is very harmful for the patient. Lastly, OIPN is one reason why, despite negative results of the IDEA trial [18], oxaliplatin-based adjuvant treatment of high-risk stage II and low-risk stage III colon cancers is now used for only 3 months as standard of care as compared the previously 6 months of adjuvant treatment.

Donepezil, a reversible inhibitor of cholinesterase, is used to treat Alzheimer’s disease and dementia [19]. Donepezil is reported to have a good safety profile in humans [20–22]. In addition, preclinical data have provided initial evidence of its effectiveness in diminishing neuropathic symptoms and related comorbidities in OIPN animal models [23, 24]. The preclinical evidence and the lack of clinical trial data led us to design the first proof of concept study to assess the efficacy and tolerance of donepezil in the treatment of OIPN in cancer survivors.

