Because of the absence of preliminary clinical results in the literature about donepezil and CIPN, and the recommendations of international experts (expertise of our project in the framework of a call for projects), we will perform a proof-of concept study to generate preliminary results for a future randomised placebo-controlled phase 3 study if the results are positive. Then, for the primary endpoint, the responder rate will not be compared to placebo, but assessed only for the donepezil arm after 16 weeks of treatment. Donepezil will be considered effective if 7 or more responders are observed in the 33 patients of the donepezil arm (see “statistics” paragraph for details). The responder rate will be compared to the placebo arm only for the secondary endpoint.

In the event of a beneficial therapeutic effect at the end of treatment (significant reduction in neuropathic disorders [reduction of one grade of neuropathy (according to NCI-CTCAE v4.0 or QLQ-CIPN20 score) or -30% of neuropathic pain (according to NRS 0–10 scale), if present, or PGIC score of 6 or 7]), the investigator will be allowed to request a lifting of the treatment blind, to adapt the further management of the patient and/or refer the patient to a specialist (neurologist, pain physician).

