### Statistical considerations

#### Sample size estimation

Fleming’s one-stage design will be used for sample size estimation. Sixty-six evaluable patients (33 by arm) will be accrued. The null hypothesis that the responder rate is 10% (maximal non-efficacy threshold, according to Smith et al*.* [43]) will be assessed against a one-sided alternative for the donepezil arm. The null hypothesis will be rejected if 7 assessable or more responders are observed in the 33 patients of the donepezil arm. This design yields a type I error rate of 0.0417 and a power of 91% for a responder rate of at least 30% in the donepezil arm (minimal clinical efficacy threshold). Thus, we have decided to include a total of 80 patients (2 × 40) to take into account lost to follow-up (20%, according to clinical practice with Alzheimer patients, which mainly corresponds to a poor tolerance at 5 mg/day dosage or when switching from 5 mg/day to 10 mg/day dosage), and possible tumor recurrence.

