#### Statistical analysis

All statistical analyses will be performed using SAS software version 9.4 before breaking the randomization codes, according to International Conference on Harmonization-Good Clinical Practice guidelines. A two-sided *p*-value of less than 0.05 will be considered for the statistical significance of all the analyses. The results will be expressed as hazard-ratios and 95% confidence intervals. Secondary analyses will be exploratory.

The baseline description of the patients included in the analysis will be carried out, without presenting inferential statistical tests (according to recommendations). As part of a proof-of-concept, only patients who have completed the study (treatment received in its entirety for 16 weeks whatever the dose = per protocol population) will be analyzed for the primary endpoint. The primary endpoint will be the rate of responders and will be described using frequency and percentage. A 95% one-sided confidence interval will also be calculated. Subgroup analyses for the primary endpoint will be planned for each stratum of the randomization (neuropathy grade, age of neuropathy and type of chemotherapy).

For the secondary endpoints, analyses will be performed on the intention-to-treat and per-protocol populations and compared to the placebo arm.

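### The responder subgroup analyses by randomisation stratum use the donepezil arm only, so they cannot separate a differential drug effect from a difference in natural course or placebo response

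*Protocol article*

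**What the plan says.** The subgroup plan is one sentence in the protocol article, Statistical analysis: "Subgroup analyses for the primary endpoint will be planned for each stratum of the randomization (neuropathy grade, age of neuropathy and type of chemotherapy". The same paragraph restricts the primary endpoint to completers: "only patients who have completed the study (treatment received in its entirety for 16 weeks whatever the dose = per protocol population".

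The section on the primary endpoint fixes which arm is used: "the responder rate will not be compared to placebo, but assessed only for the donepezil arm after 16 weeks of treatment". It then places the placebo comparison elsewhere: "The responder rate will be compared to the placebo arm only for the secondary endpoint". Study objectives and Sample size estimation agree with this.

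No subgroup analysis is attached to the secondary placebo comparison. In the comparative models the stratification factors appear only as candidate covariates. The one interaction named, for the longitudinal models, is arm by time.

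**The concern.** Randomisation is stratified by neuropathy grade, age of neuropathy and type of chemotherapy, so each stratum should hold concurrent placebo patients. The planned subgroup analyses do not use them.

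A difference between strata within one treated arm is the sum of two things: the difference in what would have happened without the drug (natural course plus placebo response), and any true difference in drug effect. One arm cannot separate them. An inert drug can seem to do better in whichever stratum improves more by itself, and a real differential effect can be masked by an opposite natural course.

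The course without treatment is not assumed to be uniform. The Background says of the neuropathy that "sometimes it continues to worsen despite stopping oxaliplatin". The inclusion criteria require at least 6 months since chemotherapy and state no upper limit. The Discussion justifies the placebo arm partly by the importance of the placebo effect. At stake is how the stratum results are read, not the trial's main decision.

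**Working it through.** **1. The plan's own figures.** Inputs from Sample size estimation: n = 33, rejection at 7 or more responders, "The null hypothesis that the responder rate is 10% (maximal non-efficacy threshold"), and "a responder rate of at least 30% in the donepezil arm (minimal clinical efficacy threshold"). The hypothesis "will be assessed against a one-sided alternative for the donepezil arm". Exact binomial tails:

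- Type I error = P(X ≥ 7 | n = 33, p = 0.10) = 0.0417, as stated.
- Power = P(X ≥ 7 | n = 33, p = 0.30) = 0.9056, stated as 91%.

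The design figures reproduce and are not in dispute.

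**2. What each contrast estimates.** Let b₁ and b₂ be the responder rates without drug in two strata, and d₁ and d₂ the drug effects.

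- Donepezil arm only: (b₁ + d₁) − (b₂ + d₂) = (b₁ − b₂) + (d₁ − d₂).
- Arm by stratum: [(b₁ + d₁) − b₁] − [(b₂ + d₂) − b₂] = d₁ − d₂.

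With an inert drug (d₁ = d₂ = 0), the first equals the whole background difference and the second is zero.

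**3. Illustrative size.** Assumptions, none given in the protocol: an inert drug, 17 evaluable donepezil patients in the better-prognosis stratum and 16 in the other, and the background rates below. With independent X₁ ~ Bin(17, b₁) and X₂ ~ Bin(16, b₂), the probability is P(X₁/17 − X₂/16 ≥ 0.20), by exact enumeration. The overall rate is (17b₁ + 16b₂)/33.

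| b₁ vs b₂ | Overall rate | P(gap ≥ 20 points) |
|---|---|---|
| 10% vs 10% | 10% | 2.4% |
| 12% vs 8% | 10.1% | 6% |
| 15% vs 5% | 10.2% | 15% |
| 20% vs 0% | 10.3% | 45% |

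These rows hold the overall rate near the design's 10% null. Wider background differences give larger figures, for example 50% at 30% vs 10% and 77% at 40% vs 10%. Those last two imply overall no-drug rates of about 20% and 25%, well above the null. At such rates the 7-of-33 rule would itself pass an inert drug in 52% and 79% of trials. That is a separate question about the single-arm null and should not be used to size this point.

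**4. Precision of the two-arm contrast.** 66 evaluable patients in four equal cells is 66/4 = 16.5 per cell. With a common rate p, the SE of the interaction (difference of two risk differences) is √(4p(1 − p)/16.5):

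- p = 0.10: SE 0.148; 95% half-width 1.96 × 0.148 = 29 points.
- p = 0.20: SE 0.197; half-width 39 points.
- p = 0.30: SE 0.226; half-width 44 points.

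**The case against.** **No claim or test of differential efficacy is planned.** The primary endpoint is to be described by frequency, percentage and a one-sided interval. The most natural reading of the subgroup sentence is a responder rate per stratum. This stands. A rejection rate for a between-stratum test would evaluate something the protocol does not specify. What remains is that stratum rates shown without their placebo counterparts invite a comparison they cannot support.

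**A reader might infer that the subgroups will choose the phase 3 population.** No section says so. The Abstract and the primary endpoint section link phase 3 only to positive results, and positivity is judged by 7 of 33 overall.

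**A reader might infer that natural course is known to differ by age of neuropathy or type of chemotherapy.** The documents do not show this. The Background links worsening to risk factors such as diabetes and alcohol, not to these strata. Worsening or persistence also does not produce responders; that takes spontaneous improvement or placebo response. The material supports a variable course, not a known difference by stratum.

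**The single-arm primary endpoint is deliberate and disclosed.** The article lists it among its main limitations. That disclosure concerns the overall result. It does not require the stratum analyses to omit placebo patients, and using stratification factors as covariates adjusts for prognosis without estimating an effect within each stratum.

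**Display by arm could be left to the analysis plan.** In general it could. Here the article names the endpoint for the subgroups, and that endpoint excludes placebo.

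**Conclusion.** The point holds as a limit on interpretation: with the donepezil arm alone, a stratum difference cannot be told apart from a difference in natural course or placebo response. That follows from the structure of the contrast and needs no assumption about rates.

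The size is unknown. The 6% and 15% figures, against 2.4% by chance alone, rest on an inert drug, an assumed 17/16 split and assumed background rates that keep the overall rate near 10%. It would be too strong to say that strata with a better course will look like strata where donepezil works better: in a single trial of this size that pattern is possible, not assured. The primary decision and the sample size are unaffected. Minor severity.

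**What to change.** Replace the subgroup sentence with wording to this effect: *For each randomisation stratum, the responder rate will be reported in both arms, with the donepezil-minus-placebo difference and its 95% CI. An arm-by-stratum interaction will be estimated as an exploratory analysis. Responder rates in the donepezil arm alone will not be used to support a claim of differential efficacy.*

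The cost is wording only. Both arms are randomised within these strata and both complete the QLQ-CIPN20, so no patients, visits or data are added. The downside is imprecision: the interaction half-width of roughly 29 to 44 points means it will rarely settle whether the effect differs by stratum, and it should be labelled exploratory.

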### Study objectives

The primary objective is to assess the curative efficacy of donepezil on the severity of OIPN in patients having received and completed oxaliplatin-based chemotherapy indicated for colorectal and pancreatic cancers and eliciting QLQ-CIPN20 sensory score ≥ 30 / 100 (equivalent to grade ≥ 2 peripheral neuropathy). Efficacy will be based on the percentage of responders (decrease of peripheral neuropathic grade according to the QLQ-CIPN20 sensory score) only in the donepezil arm (see the “Study endpoints” chapter for details).

The secondary objectives are safety (type, intensity, frequency of adverse effects and treatment discontinuation rate due to adverse effects) of donepezil, and its efficacy compared to the placebo arm, for:Neuropathic symptoms throughout the study (severity and responders),Anxiety and depression,OIPN grade,Neuropathic pain,Health-related quality of life,Patient global impression of change (PGIC),Consumption of painkillers.

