#### Exclusion criteria

◦ Ongoing cancer,◦ Pregnancy or breastfeeding (required contraception),◦ Patient with chronic progressive disease inducing pain (excluding OIPN),◦ Diabetic patient (excluding non-insulin-treated or insulin-treated diabetes of less than 5 years) or presence of a proven diabetic neuropathy◦ Other types of neuropathies,◦ ALT / AST more than 3 times the normal value,◦ Severe cardiovascular disease, bradycardia (< 55 bpm), heart conduction disorders,◦ History or active gastroduodenal ulcer,◦ Asthma or obstructive pulmonary disease,◦ Allergy to donepezil or piperidine derivatives,◦ Drug interactions: CYP3A4 inhibitors (ketoconazole, itraconazole and erythromycin); CYP2D6 inhibitors (quinidine, fluoxetine) and enzymatic inducers (rifampicin, phenytoin, carbamazepine),◦ Dependence on alcohol and/or drugs,◦ Psychotic disorders, patient under antipsychotics.

No therapeutic change will be generated by the protocol; patients will be treated with donepezil or placebo in addition to their current treatment of OIPN, if any. However, no therapeutic change for OIPN or pain will be allowed throughout the study.

Patients can discontinue the study treatment for any of the following reasons: intolerance to donepezil and significant adverse events; and can be withdrawn from analysis for any of the following reasons: modification of the antineuropathic / analgesic therapy (if any) during the study, withdrawal of consent and serious protocol deviation.

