#### Secondary endpoints

The evolution of all the secondary parameters will be studied in an intragroup (before *vs.* after treatment) and an intergroup (placebo *vs.* donepezil arm): i) Sensory, motor and autonomic scales from the QLQ-CIPN20 questionnaire (see below); ii) Grading of OIPN by NCI-CTCAE v4.0: this scale will be used to grade the severity of sensory neuropathy from 1 to 4 (1 = Asymptomatic, 2 = Moderate symptoms; limiting instrumental of Activities of Daily Living [ADL], 3 = Severe symptoms; limiting self-care ADL, 4 = Life-threatening consequences; urgent intervention indicated); iii) Assessment of neuropathic pain: monthly assessment of pain felt in the last week by 11-point NRS. This scale is used for adults and children 10 years old or older patient self-reporting of pain (score of 0 = no pain and 10 = worst possible pain). If NRS ≥ 4/10, neuropathic pain will be validated by the DN4 interview questionnaire (“*Douleur Neuropathique 4*”) will be mandatory. The interview portion of the DN4 questionnaire is a clinician-administered screening tool for neuropathic pain [59]. The questionnaire includes 7 items (YES or NO, the test is positive for a score ≥ 3/7). If the patient have a positive DN4 and a pain intensity ≥ 4/10 (NRS), neuropathic pain will be confirmed and will be characterized by the Neuropathic Pain Symptom Inventory (NPSI) questionnaire. This self-reported questionnaire assesses neuropathic pain symptoms [60], and includes 12 items; iv) HRQoL by the QLQ-C30 questionnaire (EORTC): this auto-questionnaire (EORTC) assesses the HRQoL of cancer patients, and includes five functional scales, three symptom scales, an overall HRQoL scale, and a number of additional elements assessing other symptoms; v) Anxiety and depression by the hospital anxiety and depression scale (HADS) questionnaire: this auto-questionnaire detects anxiety and depressive disorders, and includes 14 items rated from 0 to 3 (7 questions for anxiety and 7 for depression). The following interpretation is proposed for each of the two total scores: ≤ 7: absence of symptomatology; 8 to 10: suggestive symptomatology; ≥ 11: indicative symptomatology; vi) Patients’ Global Impression of Change (PGIC): PGIC [61] assesses the general effectiveness of the treatment according to the impression of patient, with the scores from 1 to 7 (from aggravated to very improve); vii) Safety: the time to treatment failure will be assess. This is the interval between randomization to treatment discontinuation for any reason. The assessment of adverse events (AEs) associated with study treatment will be also assessed by NCI-CTCAE v4.0. Any AEs will be collected daily by the patient and during the monthly visits. AEs will be categorized according to their intensity, treatment-related or not and by type. At last, viii) Assessment of painkiller consumption (if any): drug consumption for OIPN will be assessed throughout the study.

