Repeated data collected longitudinally will be analyzed by mixed models (linear or generalized linear according to dependent variable) to study the following fixed effects, arm, time and their interaction taking into account between and within patient variability (patient as random-effect, in addition to center effect) [62]. Particular attention will be paid to safety analysis (by group: type, intensity, frequency of adverse effects). Exit rates due to adverse effects will be considered as a censored data. These criteria will be estimated by the Kaplan–Meier method, compared between groups by the log-rank test, and investigated in a multivariate marginal Cox model considering center effects. The proportional-hazard hypothesis will be verified using Schoenfeld’s test and plotting residuals. Finally, to put significant results in perspective, a sensitivity analysis will be conducted to measure the impact of the missing data. A worst-case scenario will be defined as one where patients with missing data do not react to the treatment (whatever the treatment may be). Additional analyses will then be performed according to the statistical nature of missing data (missing at random or not), in particular multiple imputation or estimations proposed by Verbeke and Molenberghs [63] adapted specifically to repeated data.

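### Safety is analysed in 16-week completers as well as by intention to treat, and in completers stopping for adverse effects is zero by definition

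*Protocol article*

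**What the plan says.** Safety belongs to the secondary endpoints. Study objectives states: "The secondary objectives are safety (type, intensity, frequency of adverse effects and treatment discontinuation rate due to adverse effects) of donepezil". Under Secondary endpoints, one item begins "vii) Safety: the time to treatment failure will be assess", and the next sentence defines that time: "This is the interval between randomization to treatment discontinuation for any reason". Adverse events graded by NCI-CTCAE come under the same item.

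Statistical analysis then assigns the populations: "For the secondary endpoints, analyses will be performed on the intention-to-treat and per-protocol populations and compared to the placebo arm". No endpoint is excepted. The per-protocol set is defined in the preceding paragraph as "treatment received in its entirety for 16 weeks whatever the dose = per protocol population". The safety methods come later in the same section: "Exit rates due to adverse effects will be considered as a censored data", with Kaplan–Meier estimation, a log-rank comparison and a Cox model. No population is named at that point, so the general sentence applies.

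Two other places bear on this. Sample size estimation plans 40 patients per arm and allows for 20% loss, attributed mainly to poor tolerance. The text closing the Exclusion criteria says that patients "can be withdrawn from analysis for any of the following reasons: modification of the antineuropathic / analgesic therapy (if any) during the study"; it adds withdrawn consent and serious protocol deviation as further reasons, and does not mention safety data.

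**The concern.** A per-protocol set made up of patients who finished treatment is selected on the outcome that the safety endpoints measure. Whoever stopped early, for intolerance or because a stopping criterion listed under Placebo was met, is outside it. For "treatment discontinuation rate due to adverse effects" and for time to treatment failure, the per-protocol result is therefore fixed before any data are seen. Adverse-event frequencies in that set describe only people who tolerated 16 weeks of treatment.

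At stake is a tolerability comparison that the protocol itself asks for. Two versions are planned with no order between them, and one must show no difference in discontinuation. The primary efficacy result is also per protocol, so it would be natural to print the per-protocol safety table beside it.

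**Working it through.** The article states no numerical result for safety, so there is none to reproduce. Its design figures reproduce (the rule of 7 or more responders in 33 gives an exact type I error of 0.04170 and power of 0.9056, against 0.0417 and 91%) and are not affected by this point.

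**Step 1: membership against event**

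| Item | Content | Section |
|---|---|---|
| Condition for the per-protocol set | all 16 weeks of treatment received, any dose | Statistical analysis |
| Event for time to treatment failure | stopping treatment, for any reason | Secondary endpoints |
| Event for exit due to adverse effects | stopping treatment, for an adverse effect | Study objectives; Statistical analysis |

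The condition excludes both events before week 16. In the per-protocol set the number of events is 0 in each arm, the Kaplan–Meier curve stays at 100%, the log-rank statistic is undefined and the Cox model has nothing to fit. This step needs no assumption.

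**Step 2: size for discontinuation**

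Inputs: 40 patients per arm and 20% loss (Sample size estimation). The share of the loss due to adverse effects is not given; the text says only that poor tolerance is the main cause. I assume 50% to 100%.

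- Leavers per arm: 40 × 0.20 = 8. Completers: 40 − 8 = 32.
- Share 50%: 4/40 = 10% by intention to treat.
- Share 75%: 6/40 = 15%.
- Share 100%: 8/40 = 20%.
- Per protocol: 0/32 = 0% in every case.

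**Step 3: direction and possible size for adverse-event frequency**

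Let q be the proportion of completers with an adverse event and d the number of 40 who leave, and assume that every leaver had one. Neither q nor the last assumption comes from the documents.

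- All randomised: (q(40 − d) + d)/40. Per protocol: q. Difference: d(1 − q)/40.
- Smallest in the range q = 20% to 50%, d = 4 to 8: 4 × 0.5/40 = 5 points.
- Largest: 8 × 0.8/40 = 16 points.
- Example, q = 30% and d = 8: (0.30 × 32 + 8)/40 = 17.6/40 = 44%, against 30% per protocol.

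The direction holds if leavers have more adverse events than completers, which the protocol's explanation of the loss implies. The size is hypothetical.

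**Step 4: the withdrawal clause**

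The Exclusion criteria text has two lists. Intolerance and significant adverse events are reasons to stop treatment. Analgesic change, withdrawn consent and serious deviation are reasons to be taken out of the analysis. Patients on the second list may have taken study drug, and nothing says that their safety data stay in.

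**The case against.** The sentence that creates the problem names intention to treat first. That analysis counts every randomised patient and so every discontinuation. A reader might infer that tolerability will be judged in completers only; the documents do not support this, and no safety information is lost. The survival methods described for safety can work only in the intention-to-treat set, so the general sentence may simply be loose drafting. An empty per-protocol curve beside a full one would mislead few readers. The end-of-treatment visit (V4) is also held after early discontinuation, so the data on these patients are collected, and stopping for an adverse effect is not among the reasons for removal from analysis. All of this stands, and it makes the point minor.

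Two further inferences also go beyond the text. One is that the trial lacks a safety population: this is a condensed article, the full protocol or analysis plan may define one, and its absence here is no finding. The other is that a biased tolerability result would drive the phase 3 decision: the only stated decision rule is the responder count, and secondary analyses are called exploratory.

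What the objection does not remove is the instruction as written. It applies per protocol to safety endpoints for which that set is invalid, gives neither population precedence, and would contradict a safety set defined elsewhere. An empty curve is easy to spot, but a lower adverse-event table is not.

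**Conclusion.** Wrong as written, of minor severity. The per-protocol safety analysis is uninformative for discontinuation and time to treatment failure by definition, and probably understates adverse-event frequencies. With the protocol's own 20% loss, and 50% to 100% of it assumed to be for adverse effects, the two planned analyses would report 10% to 20% and 0% for the same arm. For adverse-event frequency, the gap of 5 to 16 points illustrates the direction under stated assumptions and is not an estimate. The withdrawal clause adds a smaller gap: as worded, some exposed patients could be removed from every analysis, safety included.

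**What to change.** In Statistical analysis, limit the per-protocol analysis of secondary endpoints to efficacy. State that adverse effects, discontinuation due to adverse effects and time to treatment failure are analysed in all patients who took at least one dose, or in all randomised patients, and that this population governs safety.

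In the text closing the Exclusion criteria, state that withdrawal from analysis does not remove safety data collected up to the date of withdrawal.

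Both are wording changes. They need no extra patients, visits or data.

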Descriptive statistics will be presented by treatment arms. Continuous variables will be presented as mean and standard deviation (otherwise as median and interquartile range) and will be compared between arms using the unpaired t test or the Mann–Whitney U test when appropriate according to the assumptions of the t-test: (i) the Shapiro–Wilk test will be used to assess normality, and (ii) the Fisher-Snedecor test to assess homoscedasticity. When appropriate (for example, for the sensory scores of the QLQ-CIPN20), these analyses will be supplemented by the recommendations proposed by Vickers and Altman, i.e. ANCOVA, considering baseline scores as covariates. Then, multiple linear mixed models could be run with centers as random-effects. Covariates will be determined according to univariate results and to their clinical relevance, including stratification parameters. The normality of residuals will be studied as described previously. If appropriate, a transformation (for example logarithmic) should be proposed to achieve the normality of dependent variable. The results will be expressed as regression coefficients and 95% confidence intervals. The analyses of other continuous secondary endpoints (11-point pain NRS, DN4 interview, NPSI, HADS and QLQ-C30 questionnaires) will be carried out similarly. For categorical parameters (adverse effects, PGIC, DN4 interview or HADS categorized according to literature), Chi-squared or Fischer exact tests will be used to compare the treatment arms. A generalized linear mixed model (more precisely logistic regression for dichotomous outcomes) will be applied for multivariable analyses. The results will be expressed as relative risks and 95% confidence intervals.

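### Secondary between-arm analyses: logistic models are to be reported as relative risks with no method that yields them, and baseline-adjusted ANCOVA only supplements a pre-tested, unadjusted test

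*Protocol article*

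**What the plan says.** All of this is in the protocol article, Statistical considerations, Statistical analysis.

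- **Dichotomous outcomes.** After chi-squared or Fisher tests, "A generalized linear mixed model (more precisely logistic regression for dichotomous outcomes) will be applied for multivariable analyses". The next sentence reads: "The results will be expressed as relative risks and 95% confidence intervals". No log link, modified Poisson model or standardisation step is named.
- **Continuous outcomes.** The arms are compared by unpaired t test or Mann–Whitney test, "when appropriate according to the assumptions of the t-test". Those assumptions are checked with a Shapiro–Wilk test and a variance-ratio F test. ANCOVA on the baseline score is an addition, used where judged appropriate; the QLQ-CIPN20 sensory score is the example given. The other continuous endpoints follow the same scheme.
- **Model covariates.** "Covariates will be determined according to univariate results and to their clinical relevance, including stratification parameters".
- **Repeated measures.** Mixed models with arm, time and their interaction are planned for longitudinal data.
- **Status.** Secondary analyses are declared exploratory. The responder comparison with placebo is one of them (Study endpoints, Primary endpoint).

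**The concern.** A logistic model estimates odds ratios. With a random effect (centre is the natural reading here) they are also conditional on that effect. Responder rates of the order discussed in this trial are too common for an odds ratio to approximate a relative risk, so the named model and the named measure do not match as written.

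For continuous endpoints, the data decide whether means or ranks are compared first, and the comparison that uses the baseline score ranks second. The randomisation factors (neuropathy grade, age of neuropathy, type of chemotherapy) and the baseline scores are known in advance, so univariate screening is not needed to find covariates.

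The primary endpoint looks at the donepezil arm alone, so these analyses are the trial's only randomised comparison of efficacy. The Discussion relies on that comparison to strengthen the evidence, and the study is meant to supply preliminary results for a phase 3 trial. A mislabelled ratio carried forward would make a phase 3 effect assumption too optimistic.

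**Working it through.** **1. The plan's own figures.** Inputs from Sample size estimation: "Sixty-six evaluable patients (33 by arm) will be accrued"; null rate 10%, alternative 30%; "The null hypothesis will be rejected if 7 assessable or more responders are observed in the 33 patients of the donepezil arm". Exact binomial with n = 33: P(X ≥ 7) is 0.0417 at 10% and 0.9056 at 30%. The stated 0.0417 and 91% reproduce. Nothing below touches them.

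**2. Odds ratio against relative risk.** RR = p1/p0 and OR = [p1/(1−p1)]/[p0/(1−p0)], so OR/RR = (1−p0)/(1−p1). The document gives no placebo rate. The first row borrows the 10% null and 30% alternative of the donepezil arm; the other rows are assumptions.

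| Placebo, donepezil | RR | OR | OR/RR − 1 |
|---|---|---|---|
| 10%, 30% | 3.00 | (0.3/0.7)/(0.1/0.9) = 3.86 | 29% |
| 10%, 20% | 2.00 | 2.25 | 13% |
| 20%, 30% | 1.50 | 1.71 | 14% |
| 20%, 40% | 2.00 | 2.67 | 33% |
| 30%, 50% | 1.67 | 2.33 | 40% |

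With no effect, both measures equal 1.

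**3. Precision from baseline adjustment.** The baseline-to-endpoint correlation ρ is not given, so it is assumed. The ANCOVA variance, as a fraction of the unadjusted variance, is 1−ρ² against final scores and (1−ρ²)/[2(1−ρ)] = (1+ρ)/2 against change scores.

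| ρ | Final scores: fraction, cut | Change scores: fraction, cut |
|---|---|---|
| 0.5 | 0.75, 25% | 0.75, 25% |
| 0.6 | 0.64, 36% | 0.80, 20% |
| 0.7 | 0.51, 49% | 0.85, 15% |

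The reciprocal of the fraction gives the sample-size equivalent. An unadjusted test would need 33%, 56% or 96% more patients against final scores (1/0.75, 1/0.64, 1/0.51), and 33%, 25% or 18% more against change scores. For an assumed effect of 0.6 SD with 33 per arm, power against final scores rises from 68% unadjusted to 80%, 86% and 93%.

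**4. Effect of the pre-tests.** The two-stage procedure was simulated with 33 per arm and no difference between arms, 4,000 runs per setting. Mann–Whitney was used if either Shapiro–Wilk test or the F test gave p < 0.05. Type I error was 0.048 (normal), 0.051 (lognormal) and 0.050 (exponential). The simulation standard error is √(0.05 × 0.95/4000) ≈ 0.003. Mann–Whitney was chosen in 15% of normal pairs and in more than 95% of skewed ones.

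**5. Effect of univariate screening.** This used 33 per arm, 3,000 runs, the baseline score always in the model, and eight pure-noise candidates kept at p < 0.2 (number and threshold assumed). With no effect, rejection rates were 0.051 at ρ = 0.3 and 0.053 at ρ = 0.6, against 0.058 and 0.052 for plain ANCOVA (simulation standard error about 0.004). At 0.6 SD, power fell from 70.2% to 66.7% at ρ = 0.3 and from 85.5% to 82.7% at ρ = 0.6, about 3 points.

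**6. Room in the responder model.** At 10% and 30% with 33 per arm, the expected number of responders is 3.3 + 9.9 = 13.2, in a trial with 26 centres. That leaves little room for screened covariates.

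**The case against.** **The relative risks may be obtained properly.** Standardisation or a log-link model would give them, the article excludes neither, and such detail often sits in an analysis plan. A reader might infer that the trial will overstate its responder effect; the text does not support that. Overstatement occurs only if an odds ratio carries the wrong label. What stands is that the article pairs a logistic model with a measure it does not produce by default.

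**Much of the remedy is already planned.** ANCOVA is foreseen for the sensory score and, by extension, the other continuous endpoints; mixed models are foreseen for repeated data. The covariate sentence also names clinical relevance and the stratification parameters, so it would be wrong to say that covariates rest on univariate results alone. This stands: the fault lies in order and conditionality, and precision is lost only if the unadjusted test is taken as the lead result.

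**The p-values are not invalidated.** A reader might infer that pre-testing and screening break the nominal error rate. The simulations show no material inflation.

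**The larger precision gains may not apply.** They assume that the unadjusted test compares final scores. The Secondary endpoints section speaks of how parameters evolve, which fits change scores; on that reading the gain is smaller at the higher correlations.

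**The 10% is not a planned placebo rate.** It is the non-efficacy threshold for the donepezil arm. Every ratio in the first table therefore rests on an assumed control rate.

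**The analyses are exploratory.** The rule of 7 responders among 33 uses none of these methods. This stands and limits the severity.

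**Conclusion.** The point holds at minor to moderate severity.

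- **Effect measure.** This is the strongest part. Model and reported measure are mismatched as written. The possible error is 29% at 30% against an assumed 10%, and 13% to 40% over the other pairs tried. It depends on mislabelling and leaves significance unchanged.
- **Lead analysis.** Choosing the test by pre-tests, and covariates partly by univariate results, makes the analysis data-dependent. In the settings simulated it did not materially raise type I error. The cost is precision if the unadjusted test leads: 25% to 49% of the variance against final scores, or 15% to 25% against change scores, for assumed correlations of 0.5 to 0.7.

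The primary single-arm conclusion is unaffected. The point still merits correction because no other part of the trial compares efficacy between randomised arms.

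**What to change.** - **Continuous secondary endpoints.** Pre-specify one main between-arm analysis: ANCOVA, or the repeated-measures mixed model already planned, adjusted for the baseline score and the three randomisation factors. Drop the Shapiro–Wilk and F tests as a way of choosing the test, and drop univariate screening of covariates. Simple tests can remain as supporting results.
- **Responder comparison.** Either report the logistic model's result as an odds ratio, or name the method that gives a relative risk and risk difference with 95% confidence intervals: standardisation from the logistic model, or a log-link or modified Poisson model.
- **Related wording.** The opening of the Statistical analysis section says that results will be given as hazard ratios. Limit that to the time-to-event analysis, so that each outcome type has one stated measure.

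The cost is a change of wording and a few lines of code, with no further data. It should be settled before the randomisation codes are broken.
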